Participants in the working time reduction group are expected to achieve a “meaningful reduction” in average weekly working time, with original pay maintained (on par with inclusion criteria of recent national cohort trials, e.g., Fan et al., 2025). The majority of participants have switched to a 4-day week, with one full workday reduced each week. However, participants are not required to implement a 4-day schedule, and a minority have adopted other forms of work-time reduction, including a 9-day fortnight with one full workday reduced every other week, two half-days per week, or shorter days. This aligns with recent international cohort trials, in which the majority of participants switched to a 4-day week but were permitted to adopt other schedules according to organizational and individual preferences (Fan et al., 2025). For participants in this group, the research programme is explicitly referred to in recruitment materials as a “*4-day week study*.” Given the heterogeneity of work patterns adopted by employers across the trial, participants undergoing working time reduction will be referred to as the “working time reduction group” throughout this paper.

Control participants do not undergo any reduction in working time between the start and end of the research period. They maintain their original work schedule and pay. For participants in this group, the programme is referred to in recruitment materials as a “*workplace wellbeing study*.” No active deception is used; participants in this group are aware they are part of a larger study in which another group is receiving a reduction in working time.

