### Measures

2.7

The following sections describe the broad method and implementation model for each measure. There are four key data collection points: baseline, trial, end-of-trial, and 6-month follow-up. For all sections below, we collect identical data at the start and end of the trial, except for the “Work Patterns Questionnaire.” As shown in Figure 1, the “Weekly Goals and Questionnaires” are collected weekly from baseline week 1 through trial week 12 (i.e., over 14 weeks) and again at the 6-month follow-up. The “Workplace and Wellbeing Questionnaires” are collected once during baseline weeks 1 and 2, at the end of the trial (week 12), and at the 6-month follow-up. The “Work Patterns Questionnaire” is collected only in the last trial week (i.e., trial week 12). Data for the three opt-in remote measures, time-use diaries, sleep diaries, and sleep watches are collected during baseline weeks 1 and 2 and again at the end of the trial during trial weeks 10 and 11 (sleep watches and diaries), or week 11 (time-use diaries). For the three opt-in in-person visit measures at the University of Sussex, blood samples, MRI scans, and the body perception measure are collected in weeks 1 and 12 of the trial period. For working time reduction participants, the in-person measures are scheduled for the time they would otherwise have spent working during weeks 1 and 12.

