#### Work pattern questionnaire

2.8.5

At the end of the trial, participants are asked to complete eight questions confirming their work patterns over the 14-week period. These questions are identical to those taken on the international trials reported by Fan et al. (2025) and Schor et al. (2022). In addition, participants are asked five qualitative questions about their experiences during the trial. The exact wording for these questionnaires is provided in the supplementary section “*Work pattern questionnaire wording*,” and a brief summary of each measure is provided in text below.

**Working days**: Participants are asked to specify how many days per week they typically worked pre-trial, providing either an exact number or an estimated average if needed. This is measured using an open-answer text box, as well as eight possible response options ranging from 0 to 7 days. The same question is asked during the trial period to ascertain if or how this has changed from pre-trial.

**Working hours:** Participants are asked to specify how many hours per week they typically worked before the trial period, excluding time spent on breaks or commuting to/from work but including time spent catching up on work during evenings or weekends. Participants are asked to provide either an exact number or an estimated average if needed. The same question is asked during the trial period to ascertain if or how this has changed from pre-trial.

**Remote working**: Three related questions are asked to determine whether participants worked remotely and whether this has changed over the trial period. This includes whether participants work remotely, and how often this typically occurred both pre-trial and during the trial.

**Annual leave:** To check any leave taken during the trial period, participants are asked to provide all dates of leave taken during the 14 - week period. In addition, we have records of annual leave sent to us via email or in out-of-office messages.

**Experiences of the trial**: Three open-response questions specifically ask participants about their experiences during the trial. This includes reflection on whether the trial has felt successful for them as an individual and for their organization as a whole. Participants are also asked to reflect on perceived benefits or challenges of working with the University of Sussex.

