In line with other working time reduction trials, we will include all participants allocated to the intervention group in the primary analyses regardless of the actual extent of their working time reduction, unless the company average reduction of working hours is < 1 h per week. In which case, their data will be excluded from the main analyses. In secondary analyses, we will investigate whether intervention effects vary by the extent of working time reduction by adding this as a moderator in the mixed-effects models. The extent of working time reduction will be calculated as the difference between participants' self-reported weekly working hours before the trial and during the trial. Working time reduction will firstly be modeled as a continuous variable (hours reduced), but we will also explore potential non-linear relationships using categorical hourly brackets. Additional secondary analyses will investigate whether other individual characteristics moderate the intervention effects, such as sex, age, and baseline score for a given measure. Each potential moderator will be evaluated separately by including the relevant interaction terms in mixed-effects models.

Due to the range of data types and the number of variables, variable-specific hypotheses and model variations (i.e., specific moderators and additional covariates) will be addressed in multiple follow-up preregistrations on the Open Science Framework (OSF). These will provide further details on each data-type analysis within the OSF project repository.

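### Whole intervention companies leave the primary analysis if their achieved reduction averages under 1 h per week, a post-baseline exclusion on one side only that is likely to favour the intervention

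*Protocol article*

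**What the plan says.** The rule is in section 3.2 (Model design) of the protocol article. The general commitment is that "we will include all participants allocated to the intervention group in the primary analyses regardless of the actual extent of their working time reduction", in line with other trials of this kind. The exception follows at once: "unless the company average reduction of working hours is < 1 h per week". The consequence is stated as "In which case, their data will be excluded from the main analyses".

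Later in the same paragraph, for the secondary moderator analysis, the extent of reduction is defined as the difference between participants' "self-reported weekly working hours before the trial and during the trial". Those hours come from the Work Patterns Questionnaire, which section 2.7 says "is collected only in the last trial week (i.e., trial week 12"). The pre-trial figure is asked for in retrospect (section 2.8.5): "Participants are asked to specify how many hours per week they typically worked before the trial period". Section 2.8.6 describes a second possible source, an end-of-trial questionnaire in which the business leader gives typical full-time hours before and during the trial. Section 3.2 does not say which of the two supplies the company average.

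On what each group is meant to do, section 2.1 says: "Participants in the working time reduction group are expected to achieve a" meaningful reduction, with no number of hours attached. For the other side: "Control participants do not undergo any reduction in working time between the start and end of the research period". No rule covers controls whose hours change.

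**The concern.** Membership of the primary analysis set depends on something that happens after the intervention starts and is reported alongside the final outcomes. Companies that adopt shorter hours and then fail to deliver them are not a random subset. Failure may reflect overload or poor fit, and the Discussion itself allows that work may intensify. The Introduction cites multinational trial evidence that larger cuts in hours went with larger gains in wellbeing. On that evidence, the companies removed are those where the least benefit would be expected.

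The removal happens on one side only, so the comparison drifts from adopters against controls towards adopters who succeeded against all controls. Employers already choose their own group, as the Discussion acknowledges. This rule adds a second selection that could be avoided.

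Two features make it weaker still. Section 2.3 says that most organizations are small, medium or micro businesses and that some participants join independently, including the self-employed. A company of one has an average equal to that person's own reduction, so for them the rule excludes on individual compliance, which the opening commitment says will not happen. The Discussion also states that analysts cannot be fully blinded to group, and the exclusion turns on data that arrive with the outcomes.

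**Working it through.** The article gives no figure for the effect of this rule, so there is none to reproduce. The check has three parts.

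**1. Is the criterion post-baseline whichever source is used?** Employee hours are collected in trial week 12 (section 2.7). Leader-reported hours are collected at the end of the trial (section 2.8.6). Both follow the intervention, so the answer is yes.

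**2. Size of the shift.** Let f be the share of intervention participants in excluded companies, δR the effect in retained companies and δX the effect in excluded ones, with participants weighted equally.

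- Effect over all adopting companies: (1 − f)·δR + f·δX
- Effect after exclusion: δR
- Shift caused by the rule: f·(δR − δX)

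The shift is zero if f = 0 or if δX = δR. It favours the intervention when excluded companies do worse, and would go the other way if they did better. With δX = 0 the estimate is multiplied by 1/(1 − f).

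The documents do not give f or δX, so f is varied and δX = 0 is assumed. For δR, the table borrows the 0.45 in section 2.1, read as a standardized between-group difference. Power is two-sided at 0.05 with 75 per group (half of 150), ignoring clustering. With exclusion, the intervention group is 75(1 − f).

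| f (assumed) | All-company effect, 0.45(1 − f) | Multiplier 1/(1 − f) | Power, all kept | Power, with exclusion |
|---|---|---|---|---|
| 0% | 0.45 | 1.00 | 0.787 | 0.787 |
| 5% | 0.43 | 1.05 | 0.745 | 0.776 |
| 10% | 0.405 | 1.11 | 0.699 | 0.765 |
| 20% | 0.36 | 1.25 | 0.597 | 0.738 |

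The starting value of 0.787 is below the planned 0.95 because this is a between-group calculation. The stated 68 per group is close to what a paired two-sided test needs at the same inputs (67). That is a separate matter and this point does not depend on it.

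**3. Can the rule create an effect where there is none?** A simulation took 12 intervention companies, an intraclass correlation of 0.1, and company reductions with SD 3 h and mean 4 or 6 h. All of these are assumptions, and the true effect was set to zero.

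- Correlation of 0 between a company's reduction and its outcome change: bias about 0.
- Correlation 0.3 to 0.5, with 5% to 16% of companies excluded: bias +0.01 to +0.05 SD.
- All companies kept: bias about 0 throughout.

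A hand check of the largest case (mean 4 h, correlation 0.5): the cut lies at (1 − 4)/3 = −1 SD, the mean of the retained part is 0.242/0.841 = 0.288 SD, and 0.5 × √0.1 × 0.288 = 0.046 SD. The simulation gave 0.046.

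**The case against.** The strongest defence is that the trial studies the exposure, not the decision to adopt it. The Abstract frames the primary outcome around participants undergoing a reduction, section 3 asks what changes after one, and section 2.1 expects a meaningful reduction. A company averaging under 1 h has arguably not delivered the exposure. This has some force, and it is a good reason to report the restricted analysis. It does not justify making that analysis primary. The same sentence commits to inclusion regardless of extent, the expected reduction has no threshold and is not screened at baseline, and individual non-reducers in retained companies stay in. The set is therefore neither all adopters nor all exposed.

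Several stronger readings are tempting but not supported:

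- **That the section contradicts itself.** It does not. The exception is explicit, numeric and published in advance.
- **That a randomized comparison is broken.** Groups are self-selected, so there is none to break.
- **That the company average rests on a few employees' recall in week 12, with a calculable misclassification rate.** The self-report formula is given for the moderator analysis, and the leader questionnaire could supply the average instead. Neither the number of respondents nor the spread of hours is stated.
- **That the lack of an all-company sensitivity analysis is itself an error.** Model variations are deferred to preregistrations not shown here.

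It is also fair that a minimum-reduction rule has no direct mirror for controls. The asymmetry remains all the same: a control company whose hours changed would stay in.

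**Conclusion.** The point stands. Section 3.2 removes whole intervention companies from the main analyses on achieved, end-of-trial reported hours, with no counterpart among controls. Given the dose-dependent benefit the article cites, the likely direction is in favour of the intervention.

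A reader might infer that the rule is certain to inflate the result. The documents do not show that. They do not say how many companies fall below 1 h or how those companies fare, and if none do the rule changes nothing. Under the assumption of no effect in the excluded companies, the estimate is 1.05 to 1.25 times the all-company effect for f between 5% and 20%. A partial benefit there would reduce the factor and harm would raise it. Because only whole companies are dropped, the bias is limited further.

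**What to change.** In section 3.2, and in the modality preregistrations still to come:

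- Define the primary analysis set as all participants in every company that entered as working time reduction, whatever hours were achieved, with all controls kept on the same basis.
- Move the < 1 h exclusion to a labelled per-protocol sensitivity analysis.
- State whether employee reports or the leader questionnaire set the company average, and how independent participants are treated.
- Report the number of companies and participants the sensitivity analysis removes.

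This costs a small edit to one paragraph and one further model run per outcome. The primary estimate may be somewhat smaller and power lower: in the illustration, 0.745 against 0.776 at f = 5%, and 0.597 against 0.738 at f = 20%.

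I would not add a baseline question on hours at this stage. Collection began in 2022 and, with one exception, control employers joined from 2025 (section 2.6). A new item would reach a larger share of controls than of intervention participants, so hours would be measured differently in the two groups.

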### Participants and inclusion criteria

2.1

The study protocol was approved by the Brighton and Sussex Medical School Research Governance and Ethics Committee (RGEC; protocols ER/BSMS6337/4 and ER/BSMS6337/6) and conducted in accordance with the ethical standards set by the British Psychological Society and the Declaration of Helsinki. The study recruits two groups of participants: those undergoing working time reduction and control participants who do not change working hours.

We aim to recruit a balanced sample of at least 150 participants for all measures (with approximately half who reduce their working time and half controls). Sample size was determined using a power calculation in G^*^Power on questionnaire pilot data (*n* = 30) with an effect size of 0.45, alpha of 0.05 and power of 0.95. This suggests a group sample size of at least 68 is required. Furthermore, participation in certain study components is voluntary (e.g., MRI, blood sample, interoception, sleep, and time-use diaries), and therefore sample sizes are expected to vary across modalities as a consequence of participant self-selection and differential uptake of specific measures; accordingly, statistical power is also expected to vary between outcome domains. However, as this is the first working time reduction trial to use non-self-report measures, it was not possible to estimate power calculations beyond questionnaire data. In addition, as we will not examine moderating subgroup effects within the control group, fewer controls may be required. The primary purpose of the control group is to account for factors unrelated to the intervention itself, including practice effects, familiarity with the MRI scanning environment, and temporal changes that may occur irrespective of working time reduction. This will allow us to determine whether observed changes in outcomes can be attributed to the working time reduction intervention rather than repeated testing or assessment effects.

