### Model design

3.2

This study uses a longitudinal mixed-effects design with a hierarchical structure. Repeated measures data are nested within employees, who are nested within companies, meaning observations are not independent and will be analyzed using multilevel methods. The design includes one between-subjects factor (group: intervention and control) and one within-subjects factor (time, which will vary per analysis with three datapoint options: baseline and end of trial; baseline, end of trial and 6-month follow-up; and the weekly questionnaires), with an interaction between time and group and corrections for multiple tests. When relevant, employee-level (e.g., age, household income) and company-level (e.g., industry, company size) covariates will be added to statistical models. Table 1 provides a list of all planned covariates. The independent variables will be fixed effects, with up to three random effects: time, employee, and organization. Covariates will be added to the model as fixed effects. This design enables us to determine whether changes are observed across time points for the working time reduction intervention group but not for controls.

**Table 1 T1:** Planned individual-level and company-level covariates for inclusion in statistical models.

Category	Covariate	Type
Individual-level	Baseline value of dependent variable	Continuous
	Gender or sex	Categorical
	Household income	Categorical
	Education level	Categorical
	Age	Continuous
	Living area	Continuous
	Job title	Categorical
	Hours of working time reduction	Continuous
	Remote work status	Categorical
Company-level	Industry	Categorical
	Company size	Categorical
	Trial start month	Categorical
	Profit status	Categorical

The specific coding scheme used for categorical variables alongside any data specific covariates will be specified in future modality-specific preregistrations.

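### Hours reduced is the treatment dose and about zero in controls by design, so testing it as a moderator of group x time does not test the dose-response

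*Protocol article*

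**What the plan says.** Section 3.2 of the protocol article describes a mixed model with group and time as factors, "with an interaction between time and group and corrections for multiple tests". The intervention effect is therefore the group x time term.

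The opening of Section 3 makes moderation by individual differences the secondary objective and lists extent of working time reduction there with sex, age and baseline score. Section 3.2 then plans to "investigate whether intervention effects vary by the extent of working time reduction by adding this as a moderator in the mixed-effects models". The variable is "the difference between participants' self-reported weekly working hours before the trial and during the trial", entered first as continuous hours and then in hourly brackets. After adding sex, age and baseline score, the section says: "Each potential moderator will be evaluated separately by including the relevant interaction terms in mixed-effects models".

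For controls, Section 2.1 states: "Control participants do not undergo any reduction in working time between the start and end of the research period". Section 2.8.5 nevertheless puts the questions on hours before and during the trial to participants generally, so controls will have reported values too.

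Two other places bear on the point. Section 2.1 remarks, in justifying the size of the control group: "as we will not examine moderating subgroup effects within the control group, fewer controls may be required". Table 1 lists "Hours of working time reduction" among the planned individual-level covariates.

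**The concern.** Sex, age and baseline score exist in both groups before the intervention, so group x time x moderator is the right term for them. Hours reduced is what the intervention changes. It varies in the reduction group, while in controls it should consist only of reporting error and incidental change around zero.

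Put through the same interaction, it answers a different question: does outcome change per hour differ between groups? A real dose-response could then be reported as an effect that does not vary with the extent of reduction. The group x time coefficient printed beside it, with hours uncentred, would be the group difference at zero hours reduced. That is not the intervention effect. Extent of reduction is the first moderator that Section 3.2 develops, so the secondary objective is directly affected.

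**Working it through.** The article gives no power or precision figure for the dose analysis, so there is none to reproduce.

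**What the term estimates.** With two time points, write the change from baseline to end of trial as

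change = b0 + b1·group + b2·hours + b3·group·hours.

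In the repeated-measures model, b1 is group x time, b2 is time x hours and b3 is group x time x hours. The control slope is b2 and the reduction-group slope is b2 + b3. Three consequences follow.

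- With a common slope, b3 = 0 whatever the size of b2. For example, take 0.075 SD per hour in both groups and a mean reduction of 6 h. The effect at the mean dose is 6 × 0.075 = 0.45 SD, yet b3 is zero. So is b1, because hours already carries the whole effect.
- With hours uncentred, b1 is the group difference at zero hours.
- With hourly brackets, controls should sit almost entirely around zero, leaving group-by-bracket cells empty or nearly so.

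**Power when the control slope is zero.** Inputs:

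- 75 per group, from the target of at least 150 split about equally in Section 2.1.
- Assumed, because the article does not give them: SD of hours s1 = 3 h in the reduction group; control SD s0 from 0.5 to 3 h; residual SD of change σ; two-sided 5% level; no clustering.
- A slope set so that the test within the reduction group has 78% power.

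Within the reduction group, SE = σ/(s1·√n1) = σ/(3 × 8.66) = 0.0385σ. For 78% power the slope is (1.96 + 0.77) × 0.0385σ = 0.105σ per hour.

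For the three-way term, SE(b3) = σ·√(1/(n1·s1²) + 1/(n0·s0²)).

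| Control SD (h) | SE(b3)/σ | slope/SE | Power, three-way | Power, within group |
|---|---|---|---|---|
| 0.5 | 0.234 | 0.45 | 7% | 78% |
| 1 | 0.122 | 0.86 | 14% | 78% |
| 2 | 0.069 | 1.52 | 33% | 78% |
| 3 | 0.054 | 1.93 | 49% | 78% |

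Simulation (4,000 trials per scenario) gave 7%, 14% and 32% at 0.5, 1 and 2 h. With equal slopes in both groups it gave 4–5%, which is the false-positive rate.

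**Other slopes.** The same formulas, for control SDs of 0.5, 1, 2 and 3 h:

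- Slope 0.075σ per hour (0.45 SD at 6 h): 6%, 10%, 19% and 28%, against 50% within group.
- Slope 0.15σ per hour (0.9 SD at 6 h): 10%, 23%, 58% and 79%, against 97% within group.

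**All control values exactly zero.** The hours and group·hours columns then coincide (design rank 3 of 4). With one dropped, the remaining term is the reduction-group slope. Simulated power is 48% and 97% for the two slopes just given, so nothing is lost.

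**The case against.** The strongest reply is that the article never writes out a three-way term. It speaks of relevant interaction terms, which for a dose could be time x hours. The remark in Section 2.1 that moderation will not be examined within controls fits an analysis of the reduction group alone, and a mixed model can be fitted in one group. Section 3.2 also leaves model variations to later preregistrations.

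Much of this stands. The three-way term is the plain reading, not a stated formula. But Section 3.2 already fixes the dose variable, its calculation, its forms and its role as a moderator of the intervention effect, and it does not limit the analysis to the reduction group. The Section 2.1 remark is made to justify fewer controls. If it is meant to define the dose analysis, Section 3.2 should say so.

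A reader might also infer that the planned test has almost no power. The documents do not support that as a general statement. They give no SD of hours in either group, and power reaches 49% in the main scenario at a control SD of 3 h, and 79% with the steepest slope. Section 2.8.5 counts evening and weekend catch-up work, so real variation among controls is possible. Nor is the case of all-zero control hours a harm: the term is aliased, but the slope is still recovered.

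**Conclusion.** The point holds as a mismatch between the question and the term. Read literally, the planned moderator compares dose slopes between groups. It is null under a common slope, and it turns the uncentred group x time coefficient into an effect at zero dose.

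The size of the power loss is conditional. With a zero control slope and the main assumptions above, the loss against the within-group test is 71, 64, 45 and 29 percentage points at a control SD of 0.5, 1, 2 and 3 h (78% less 7%, 14%, 33% and 49%). With a common slope only the 5% false-positive rate remains. With control hours all exactly zero there is no loss.

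A reader might carry this over to the primary analysis. The group x time comparison is not affected, unless hours reduced is entered in that model as a Table 1 covariate. The group coefficient would then be conditional on the dose. The defect lies in a secondary analysis, but the document fixes that analysis in an unsuitable form, and the change is worth making before the preregistrations are written.

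**What to change.** In Section 3.2, and in the list of moderators at the opening of Section 3:

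- Take hours reduced out of the moderators of group x time.
- Estimate dose-response as time x hours reduced among reduction-group participants, continuous first and then in brackets. This agrees with the remark on controls in Section 2.1.
- Keep the group contrast in its own model, without hours reduced as a covariate, and note this against the entry in Table 1.
- Label the dose result as observational, because the amount of reduction is not randomised.
- Leave sex, age and baseline score as moderators of group x time.

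The cost is a change of wording and a simple model. No new data are needed. The small downside is that the dose result is reported as an association within the reduction group.
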